#### Anthropometry

Anthropometric measurements included height (m), weight (kg), body mass index (BMI) (kg/m^2^) and waist circumference (cm). Standing height and body mass were measured to the nearest 0.1 cm and 0.1 kg respectively with a SECA 763 digital column scale (SECA Ltd., USA). Waist circumference was measured at the narrowest part of the waist by a Lufkin steel tape measure to the nearest 0.1 cm. All measurements were conducted according to standardised ISAK techniques [67].

#### Body composition

Body Composition was measured using the BOD POD (air displacement plethysmography) (COSMED Asia-Pacific Pty Ltd., Artarmon NSW) The BOD POD uses whole-body densitometry to determine body composition in terms of fat and fat-free mass. All participants who opted for level 2 and above, underwent two tests at each visit lasting approximately 50 s each. The same BOD POD machine was used throughout the study and was calibrated and maintained as per the manufacturer’s recommendations. In some cases, additional measurements of regional and whole-body lean mass and fat mass were derived from a whole-body scan with Dual-Energy X-ray Absorptiometry (DXA) (Hologic 4500A Discovery, Hologic Corp., Waltham, MA, USA). The level of radiation exposure from the DXA scans was negligible (10–30 microSieverts [μSv] in comparison to a flight from Perth to London, approximately 100 μSv). The number of scans conducted in this study were well within the guidelines provided by the manufacturer of the DXA. The scans were conducted by a qualified operator using the same machine each time, however as only a limited number of participants underwent these tests, the results are for reference only.

Due to the inability to relocate the BOD POD machine, participants who attended regional clinics had their body composition, fat mass and fat-free mass measured to the nearest 0.1% using a transportable Impedimed Imp DF50 (Impedimed Ltd., QLD) tetrapolar bioelectrical impedance analyser (BIA). For this procedure participants were asked to lie in a supine position and four electrodes were placed on their hands and feet. A weak electrical current was passed through their body (which they could not feel) and readings from this were used to calculate fat mass, fat-free mass and body water. Reliability of body composition can be influenced by level of hydration. Participants were asked to attend the clinics well hydrated, to refrain from water/fluid ingestion for 1 h prior to the scan and void their bladder.

#### Blood pressure

An Omron IA1B Automated Blood Pressure Device (Omron Healthcare Ltd., Japan) was used to measure participants’ blood pressure. Readings were taken in triplicate with the participant in a calm and relaxed state, in a seated position, on their arm at heart level, at 1-min intervals. All three readings were recorded with the lowest to be used in analysis.

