### Primary and secondary outcomes and endpoints

The primary outcome of cooking confidence was evaluated via the theoretical concept of personal beliefs of self-efficacy measured across five areas:
Confidence about being able to cook from basic ingredients;Confidence about following a simple recipe;Confidence about preparing and cooking new foods and recipes;Confidence that what is cooked will “turn out” well; andConfidence about tasting foods not eaten before.

This was performed using the same method as described by Flego et al. [42] by measuring cooking confidence as a proxy for self-efficacy. The questions used were based on works by Short (2003) and Barton (2011) and presented on a 5-point Likert confidence scale ranging from ‘not at all’ to extremely’ confident. This was explored in terms of change over time and between different study groups.

The secondary endpoints were measures of dietary intake, physical activity and mobility levels, body composition, anthropometry, blood, urine and faecal biomarkers of systemic, physical and mental health and are further explained in the sections below. These were also explored in terms of change over time and between different study groups.

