### Sample size

The sample size calculation in this study was based on the findings of the first published quantitative evaluation of Jamie’s Ministry of Food (JMOF) program into its impact on participants’ cooking confidence [42]. Flego et al. reported an increase of > 0.53 on a 5-point Likert scale across all confidence items, which corresponded to a large Cohen’s effect (d > 0.8), whilst no significant changes were observed in the Control group (all *p* > 0.13). Using G*Power, the required sample for a mixed-model analysis of variance test (ANOVA) design (2 groups, each with 2 time points) to detect (conservatively) a small-medium, within-between, interaction effect (Cohen’s *f* = 0.15), at the 5% level of significance and 80% power was 90, or 45 per group. However, Flego et al. [42] noted that the participant retention rate in the JMOF program at T2 was 55% (694 at T1 and 383 at T2). To account for this and to ensure sufficient participation numbers at the end of T2, the aim was to recruit a minimum of 164 participants with 87 in each time-point (i.e. T1 and T2) of the intervention arm. No power calculation to account for T3 samples size was conducted as the investigation was not aiming to detect a change, rather, whether the effect was maintained at T3.

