### Data collection schedule and measures

At all levels of contribution, intervention participants were surveyed at three time points: before the program start (IT1), on program completion (IT2), and 6 months after program completion (IT3). Control participants were surveyed at two time points: 6 weeks prior to program commencement (CT1) and on entry to the program (CT2) (Fig. 1). Computer programmed ‘rules’ automated this process. The ECU SRC ensured consent prior to participation in the study and distributed the online survey assessment using Voxco CATI© Software [47]. The ECU SRC complies with the AMSRS Code of Professional Behaviour and since 2008 SRC has been an ISO20252 standards accredited organisation. All projects undertaken by ECU SRC are conducted in full compliance with the Interviewer Quality Control Australia (IQCA) as recommended by the Australian Market Research Industry and NHMRC/AVCC guidelines on research practices. Postal versions of all documentation were sent to persons who did not have a working email address or access to a computer. The ECU SRC sent participants their online questionnaire 1 week prior to T1, T2 and T3 (for intervention) and if necessary, they received a second reminder email during the week of T1, T2 or T3 as well as a clinic appointment reminder where applicable.

Four levels of contribution were offered to all WA adults registered on the program database (Table 1). The minimum level of contribution, completed by participants at all levels at each time point, consisted of the basic online survey evaluation used in Victoria and NSW [42–45] with the incorporation of additional assessments. These included, quality of life measured using the SF-12® Health Survey [48], wellness using the Subjective Vitality Scale [49, 50] and the Warwick-Edinburgh Mental Well-being Scale (WEMWBS) [51], and physical activity determined using the International Physical Activity Questionnaire (IPAQ) self-administered short-form [52] and the Godin Leisure-Time Exercise Questionnaire [53] (Additional file 1). Those who chose to contribute at level 2 completed the above questionnaire and also attended a clinic appointment at each time point, where they underwent dietary, anthropometric, body composition, blood pressure, timed “Up & Go” [54] and hand grip strength [55] assessments.

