#### Grip strength

Hand grip strength (kg) was obtained using a Jamar Analogue Hand Dynamometer on the dominant hand [55]. The participant stood with arms by their side and elbow bent at 90 degrees and when instructed to do so, squeezed the dynamometer with as much force as possible. Three trials lasting 3 s each were completed with 15 s rest between them and the maximum value was used for analysis.

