### Statistical methods

The computer software package IBM SPSS Statistics for Windows version 25.0 (Armonk, NY: IBM Corp) will be used to access the data set and perform the statistical analyses. For the basic online evaluation questionnaire, general descriptive analyses including frequency data with appropriate plots and cross-tabulations will be used to explore and summarise outcome variables. Continuous demographic and baseline characteristics will be summarised using standard statistics (mean and standard deviation) and non-parametric statistics (medians and inter-quartile ranges) where appropriate. Independent *t*-test for normally distributed data, and Mann-Whitney U test for non-normal data, will be used to assess differences between the groups. Frequencies and percentages will be reported for categorical variables and Chi-square test will be used to test for differences in proportion between the groups. The magnitude of change both within and between the intervention and control groups will be assessed using mixed-model ANOVA. Furthermore, changes within the intervention group will be assessed across three time points IT1, IT2 and IT3 using repeated-measures ANOVA. To account for multiple outcomes, the Benjamini-Hochberg correction (i.e. false discovery rate) will be applied to the raw *p*-values. Participants with missing value for the variables of interest (either outcome or predictor) will be removed from the repeated-measures ANOVA models. Specific demographic factors of interest (including but not limited to, gender, age, education, BMI and employment) will be adjusted for in all models. Statistical significance will be indicated at the 10, 5 and 1% level. Cohen’s effect sizes will be provided as a measure of practical/clinical significance and to assist in the interpretation of said ‘statistically significant’ results.

To interpret gut microbiota diversity and to analyse the microbial composition of the gut microbiota, multivariate analysis using a combination of R and PRIMER7 and Permanova+ (PRIMER-E, Plymouth) [82] will be conducted. Principal Coordinates Analysis (PCoA) will be deployed to visualise findings. Distance-based linear models (DISTLM) and distance-based redundancy analysis (dbRDA) will be used to integrate microbiome findings with other relevant data (i.e. dietary intake) that help explain the relationship between the microbiome findings and other outcomes.

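### Analysing the lowest of three recorded blood pressure readings gives up some precision and lowers reported levels; an average of the same readings would serve better (minor)

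*Protocol article*

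**What the plan says.** The Blood pressure section describes an automated device and readings one minute apart: "Readings were taken in triplicate with the participant in a calm and relaxed state, in a seated position". It then fixes the analysed value: "All three readings were recorded with the lowest to be used in analysis". It does not say why the lowest is chosen, or whether the lowest is found separately for systolic and diastolic pressure.

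Blood pressure is a clinic measure for participants at level 2 and above. Under Data collection schedule and measures, these participants "attended a clinic appointment at each time point, where they underwent dietary, anthropometric, body composition, blood pressure", among other tests. For the secondary endpoints, the outcomes section says: "These were also explored in terms of change over time and between different study groups". Under Statistical methods, "The magnitude of change both within and between the intervention and control groups will be assessed using mixed-model ANOVA", and a repeated-measures ANOVA across IT1, IT2 and IT3 is planned within the intervention group. The statistical analyses are described in the future tense.

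**The concern.** The minimum of several readings is an extreme-value statistic. It depends on one reading and on the spread of the other two, so it has two weaknesses that an average does not share.

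- **Precision.** Its sampling variance exceeds that of an average of the same readings. Comparing groups does not remove this.
- **Dependence on spread.** Its expected value falls as within-visit variability rises. Reported levels come out low, and a change in variability between visits would look like a change in pressure.

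The clinic measures come only from volunteers at level 2 and above, and the sample size section concerns cooking confidence alone, so there is no planned margin of precision for blood pressure. The rule for grip strength offers no parallel: "Three trials lasting 3 s each were completed with 15 s rest between them and the maximum value was used for analysis". That test asks for maximal effort, so the maximum is its target. Blood pressure is read at rest, where the target is the usual resting level.

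**Working it through.** The article states no blood pressure figure, so there is none to reproduce.

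**Inputs.** From the article: three readings per visit, with the lowest analysed. Assumed, because the article gives neither: within-visit SD of a single reading s = 4 to 8 mmHg, and visit-to-visit SD v = 6 to 8 mmHg.

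**Step 1: one visit.** For three independent normal readings around the person's level, the standardised minimum has density 3φ(x)[1 − Φ(x)]². Numerical integration gives mean −0.846 and variance 0.559.

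| Summary | Expected shift | Error variance |
|---|---|---|
| Lowest of three | −0.846s | 0.559s² |
| Mean of three | 0 | s²/3 = 0.333s² |
| Mean of two | 0 | s²/2 = 0.500s² |

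The within-visit variance ratios are 0.559/0.333 = 1.68 and 0.559/0.500 = 1.12. The level shift is 0.846 × 4 = 3.4 mmHg to 0.846 × 8 = 6.8 mmHg.

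**Step 2: change between two visits.** The variance of change is 2(v² + within-visit error variance), so the factor 2 drops out of the ratios.

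- Smallest effect, s = 4 and v = 8: minimum 64 + 8.95 = 72.95; mean of three 64 + 5.33 = 69.33; mean of two 64 + 8 = 72. Ratios 1.052 and 1.013.
- Largest effect, s = 8 and v = 6: minimum 36 + 35.81 = 71.81; mean of three 36 + 21.33 = 57.33; mean of two 36 + 32 = 68. Ratios 1.252 and 1.056.

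Square roots give the standard errors: √1.052 = 1.026 to √1.252 = 1.119 against the mean of three (about 3 to 12% larger), and √1.013 = 1.007 to √1.056 = 1.028 against the mean of two (about 1 to 3% larger).

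**Step 3: a change in s with no true change in pressure.** The minimum moves by −0.846(s₂ − s₁). If s falls from 6 to 4 mmHg, that is −0.846 × (−2) = +1.7 mmHg. An average of exchangeable readings does not move.

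**Step 4: readings that fall across the visit.** The readings are consecutive, so the exchangeable model may fail. Assume rises above the settled level of +5/+2/0 to +10/+4/0 mmHg over readings 1, 2 and 3, with s = 3 to 8.

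- The minimum lies 0.4 to 4.8 mmHg below the settled level, by simulation.
- The mean of three lies above it by (5 + 2 + 0)/3 = 2.3 to (10 + 4 + 0)/3 = 4.7 mmHg.
- The mean of readings 2 and 3 lies above it by (2 + 0)/2 = 1.0 to (4 + 0)/2 = 2.0 mmHg.
- The variance of the minimum is 1.7 to 2.4 times that of the mean of three.

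**Step 5: a first-reading rise that varies between people.** Assume a mean rise of 5 mmHg at reading 1, an SD of 3, 5, 8 or 12 mmHg, 40% of the rise remaining at reading 2, and s = 3, 5 or 8. The minimum is noisier than the mean of three in 9 of the 12 combinations. The exceptions are s = 3 with rise SD 5, 8 or 12 (variances 8.3 v 8.5, 15.1 v 17.0 and about 33.5 v 34.4). The mean of readings 2 and 3 is less noisy than the minimum in all 12.

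**The case against.** **The size of the level bias depends on the model.** The figure of 0.85s assumes exchangeable readings. If first readings run high, the minimum can be closer to the settled level than the mean of three (Step 4). This stands. A reader might infer that reported pressures are definitely 3.4 to 6.8 mmHg too low. The article gives neither s nor any reading-order pattern, so it does not support that.

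**The mean of three has its own artefact.** Suppose familiarity with the clinic shrinks the first-reading rise from +10/+4/0 to +5/+2/0, with s = 4 to 8 and no true change. The mean of three then shifts by 2.3 − 4.7 = −2.3 mmHg (−7/3 before rounding), the minimum by −0.8 to −1.4, and the mean of readings 2 and 3 by 1.0 − 2.0 = −1.0. From +5/+2/0 to no rise, the shifts are −2.3, −1.7 to −2.0, and −1.0. This also stands. It bears on which average to choose. It does not rescue the minimum, which shifts too and is less precise than the mean of readings 2 and 3.

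**The planned contrasts are changes.** A constant shift cancels from them. A reader might infer that the rule biases the estimated intervention effect. It does so only if within-visit variability or the reading-order pattern changes differently between groups, and nothing in the article indicates that. The within-group analysis over IT1 to IT3 has no control at IT3 to remove a drift, but that limit applies to any summary of the readings and does not by itself favour an average.

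**Blood pressure is peripheral.** The primary outcome is cooking confidence. Blood pressure is not named in the list of secondary endpoints, is measured only at level 2 and above, and plays no part in the sample size, which was set for the primary outcome ("at the 5% level of significance and 80% power was 90, or 45 per group"). The article sets no blood pressure threshold or eligibility rule that a level shift would affect. This stands and settles the severity.

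**Conclusion.** The point holds as a minor one. Against the mean of three, the lowest reading has 1.68 times the within-visit error variance, which becomes a 5 to 25% larger variance of change once visit-to-visit variation is counted. Against the mean of two, the loss is only 1 to 6%. These ranges rest on independent normal readings and on the assumed SDs. The gain over the mean of readings 2 and 3 held in every falling-reading scenario examined. The gain over the mean of three failed in three of the twelve varying-rise scenarios.

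The downward shift of about 0.85s affects reported levels under exchangeable readings. It enters change estimates only when s differs between visits or groups, for example +1.7 mmHg if s falls from 6 to 4 mmHg. No conclusion about the primary outcome is touched.

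**What to change.** Before blood pressure is analysed, replace the sentence on the lowest reading with a prespecified average of the recorded readings, calculated separately for systolic and diastolic pressure. Either the mean of readings 2 and 3 or the mean of all three is defensible. The first is less exposed to a raised first reading, and the second is more precise if there is no such rise. Name one as the main analysis and keep the lowest reading as a sensitivity analysis. The stored readings can first be inspected by reading order, without reference to group, to inform the choice. Stating that the two pressures are handled separately also removes the present ambiguity.

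The cost is one sentence and one recomputed variable, since all three readings were kept. The downsides are that reported levels will be a few mmHg higher than under the current rule, and that the mean of three would carry any first-reading rise and its habituation.

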#### Timed “Up & Go” test

Dynamic balance and agility (i.e. functional mobility) were measured using the timed “Up & Go” test [54]. The test quantifies the time it takes to stand up from a seated position in a ‘standard’ chair and walk around a mark placed 3 m from the chair, and then sit back down on the chair. Timing was started as the participant stood up and was stopped once they were re- seated clearly on the chair in an upright position. After familiarisation, one properly executed trial was allowed with time recorded and reported to the nearest 0.01 s.

#### Grip strength

Hand grip strength (kg) was obtained using a Jamar Analogue Hand Dynamometer on the dominant hand [55]. The participant stood with arms by their side and elbow bent at 90 degrees and when instructed to do so, squeezed the dynamometer with as much force as possible. Three trials lasting 3 s each were completed with 15 s rest between them and the maximum value was used for analysis.

#### Measures of biochemistry and urinalysis

Cumulating on level 2 assessments, those who selected the third level of contribution also provided blood and urine samples for biochemical analysis at each time point. Blood and urine samples were collected by trained phlebotomists in the morning after an overnight fast. The venous blood samples were centrifuged and processed within 30 min after collection to separate plasma and serum. These were then aliquoted into 1.5 or 2 mL vials and stored at − 80 degrees until analysis. Biochemical variables related to cardiovascular, liver, cognitive and musculoskeletal disease such as fasting blood lipids, glucose and high sensitivity C-reactive protein will be measured by routine laboratory methods. Carotenoid concentration (α-carotene, β-carotene, lycopene, β-cryptoxanthin, lutein) will be analysed as objective indicators of fruit and vegetable intake [68]. Participants gave their permission for future analyses that include the following but are dependent on available funding; advanced glycation end products (IgG *N*-glycans) measured to assess early signs of health risks such as hypertension, inflammatory diseases and cardiovascular diseases [69]; serotonin and lipopolysaccharide (LPS) as biomarkers of mental and gut health [70, 71].

#### Human faecal sample collection, processing and analysis

The fourth and maximum level of contribution incorporated the additional provision of a 24-h stool sample at each time point. Instructions and equipment were provided for the collection of stools from all bowel motions over a 24 h period, if more than one stool sample was collected, they were homogenised as individual samples and then pooled and homogenised again. This was done to provide a more accurate, homogenous measure of the gut microbiota and gut metabolites. Participants were given a portable cooler bag and frozen icepacks to store the stool samples over the 24 h collection period and to return their sample(s) to the clinic. Once received the frozen stool samples were weighed and stored at − 80 degrees. Stool samples were thawed in a fridge (max 4 °C) and homogenised before being aliquoted for various analyses. Stool aliquots for short chain fatty acids (SCFA), bile acids and microbial analysis remain at − 80 °C until their analysis.

Microbial analyses will be performed at the WA Human Microbiome Collaboration Centre, Perth WA. DNA will be extracted using the QIAamp PowerFecal DNA kit (Qiagen) using Qiacube extraction platform. Bacterial signatures are generated using the Illumina MiSeq platform using uniquely barcoded 16S rRNA gene primers (515–806(V4)), following polymerase chain reaction (PCR) inhibition assessment of each DNA extract. PCR-free ligation protocol is thereafter deployed for library building. Samples will be sequenced to a depth of minimum 50,000 reads, which is sufficient to identify microbes to a genus/species level. Quality control and mock community samples are included in the analysis from sample collection to sequence analysis. Sequence read quality is initially assessed with FastQC before demultiplexing and pre-processing by GHAPv2, an in-house tool. Cutadapt [72] is used for removal of all non-biological sequences. DADA2 [73] is then used for quality filtering, error correction and amplicon sequence variants (ASVs) picking. A trained naïve bayes classifier then assigns the ASV’s to genus/species against a curated database of microbial reference sequences such as the RDP [74] or Genome Taxonomy Database [75].

Measures of dietary fibre and protein fermentation in the stool samples will be determined from short chain fatty acids (SCFA) using gas chromatography mass spectrometry at ECU. SCFA in faecal material will be extracted into an acidified aqueous methanol solution and the SCFA separated by gas chromatography using a fatty acid column (Zebron ZB-FFAP 30 m × 0.53 mm × 1 μm supplied by Phenomenex). The SCFA will be detected using mass spectrometry and their concentrations determined by the method of internal standards. Isotopically internal standards will be spiked into the extraction solution.

As high fat diets have been associated with poorer health outcomes, in addition to blood lipids, high performance liquid chromatography in tandem with mass spectrometry will be used to analyse faecal bile acids. Beyond their role of facilitating fat digestion, recent research discoveries have emphasised the importance of bile acid metabolism as a regulator of human physiology and central to overall health [76, 77] and disruptions to BA processing are associated with the onset of chronic disease. The target bile acids will be extracted from the faecal material by solid phase extraction and then injected into a C18 column. The separated bile acids will be identified and quantified by mass spectrometry using a method developed by ECU and adapted from [78, 79]. The method of internal standards will be adopted to correct for matrix effects.

The SPIRIT figure for study protocols is presented in Fig. 3 and the 33 item SPIRIT checklist in Additional file 2 (separate upload) [80, 81].

